## 2. Experimental Design

### 2.1. Trial Design

This study has been prospectively registered on ClinicalTrials.gov under the identifier AUTH-CORE-STUDY NCT07025395, ensuring transparency and alignment with international standards for interventional research protocols.

The present study protocol has also been developed and reported in accordance with the SPIRIT 2013 Statement (Standard Protocol Items: Recommendations for Interventional Trials) [39], which provides guidance for the essential content of clinical trial protocols. Furthermore, the protocol adheres to the Template for Intervention Description and Replication (TIDieR) checklist and guide [40] and the Consensus on Exercise Reporting Template (CERT) [41], ensuring comprehensive, transparent, and replicable documentation of the core training intervention.

All completed checklists (SPIRIT, TIDieR, CERT) and the ClinicalTrials.gov registration certificate are available to reviewers and readers in Supplementary File S2. The official approval letter from the Ethics Committee is provided separately in Supplementary File S3.

This study employs a two-parallel group randomized controlled trial (RCT) design. The experimental group will undergo structured core training, while the control group will continue regular physical activity without targeted interventions. Detailed descriptions of exercise parameters, progression models, training environment, and measurement techniques are provided to enhance transparency and reproducibility.

The study protocol has been reviewed and approved by the Local Ethics Research Committee of the School of Physical Education and Sport Science at Serres, Aristotle University of Thessaloniki (Approval Code: ERC-013/2025, issued on 11 March 2025), in accordance with the University’s Code of Ethics for Research Involving Human Participants, the principles of the Declaration of Helsinki [42], and the EU General Data Protection Regulation (GDPR-EU 2016/679). All participants will provide written informed consent prior to their involvement, and personal information will be handled confidentially.

### 2.2. Study Setting

This study will take place in two distinct locations to ensure both controlled measurement conditions and practical application of the intervention. All pre- and post-intervention assessments will be conducted at the Laboratory of Neuromechanics, Department of Physical Education and Sport Science, Aristotle University of Thessaloniki in Serres, Greece. This laboratory is equipped with advanced measurement systems, including electromyography (EMG), ultrasound imaging, force plates, and biomechanical motion analysis tools, allowing for precise data collection under standardized conditions. Testing sessions will be scheduled at fixed intervals to maintain consistency in environmental factors and optimize the accuracy of results. The eight-week core training protocol will be carried out in two designated gyms in the city of Serres, both selected based on their suitability for structured strength and stability training. These gyms are specially equipped with basic tools such as resistance equipment, mats, exercise aids, and time-recording technology that facilitate the correct execution of exercises and the integrity of the intervention. All training sessions will be supervised by certified physical activity specialists who will ensure adherence to the study’s protocol and proper technical execution. The study is scheduled to begin in September 2025 and conclude in January or February 2026, following a structured timeline that ensures compliance with research design and minimizes external variability in training conditions. 

### 2.3. Eligibility Criteria

Participants for this study will be healthy, physically active adults between the ages of 25 and 35, engaging in regular recreational exercise or non-competitive sports activities. For the purpose of this study, the term “recreational exercise” was defined as physical activity engaged in a minimum of three times per week for a duration of at least one hour in each training session. A list of suitable activities is provided below, including but not limited to: aerobics, dance, folkloric dance, and swimming. A variety of outdoor activities and adventure sports are available, including orienteering, surfing, snowboarding, and caving. Racket games encompass a variety of sports, including tennis, paddle tennis, badminton, and squash. The participants were permitted to engage in a range of activities, including but not limited to mountain biking, mountain climbing, athletics, bowling, horseback riding, skateboarding, swimming, and hiking. Additionally, any other forms of exercise that the investigators deemed appropriate were permitted. In order to qualify for participation, an individual must have been continuously enrolled in the relevant programs for a minimum period of two years [41]. Inclusion is based on criteria ensuring suitability for core training interventions and reducing confounding variables related to prior structured stability training. Eligible participants must be in optimal health, demonstrating no recent musculoskeletal injuries or pre-existing conditions that could limit the full range of motion or prevent engagement in high-intensity exercise protocols. They must also commit to attending both baseline and final assessments and adhering to the structured eight-week intervention timeline to maintain data integrity.

Exclusion criteria include individuals diagnosed with musculoskeletal impairments that restrict functional movement or prevent core-specific engagement. Additionally, those with cardiovascular or metabolic conditions that contraindicate high-intensity exercise are excluded from participation. To maintain study validity, individuals already engaged in structured core training programs—such as Pilates, CrossFit, calisthenics, or athletes following systematic strength and stability regimens—will also be excluded to prevent prior training effects from influencing study outcomes.

### 2.4. Recruitment

Potential participants will be informed about the study through targeted outreach, including social media campaigns and physical posters placed in high-traffic locations such as gyms, sports facilities, and university premises. Individuals expressing interest will undergo an initial contact phase, where they will be provided with study information and invited to a one-on-one screening meeting with the research coordinator. This meeting will determine eligibility based on inclusion criteria, ensuring suitability for participation. Once eligibility is confirmed, participants will be thoroughly briefed on the preliminary and final screening procedures and asked to provide written informed consent for participation. However, the specific details of the eight-week core training protocol will not be disclosed at this stage to minimize potential bias. When the required number of participants is met, a computer-generated randomization process will allocate individuals into either the experimental group, which will undergo structured core training, or the control group, which will continue regular physical activity without targeted core interventions.

The experimental group will receive details of the training after randomization, and participants will need to sign additional written consent confirming their commitment to the intervention. The control group will receive written guidelines for a standardized two-day-per-week abs and back routine, and the program ensures controlled engagement without interfering with the core-specific intervention administered to the experimental group. Replacement participants will be recruited following the same screening and randomization procedures to maintain study integrity and adhere to predefined sample size calculations, in the event of participant withdrawal or noncompliance.

All participants will provide written informed consent prior to enrollment, and personal data will be handled in strict compliance with GDPR regulations to ensure confidentiality and participant protection (see Supplementary File S4).

A schematic representation of the planned participant trajectory (screening, eligibility, randomization, intervention, and follow-up) is illustrated in Figure 1. This flowchart is hypothetical and reflects the intended study structure prior to actual recruitment. No participant data is included at this stage, since enrollment is scheduled to begin in September 2025.

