### 3.5. Statistical Analysis

All statistical analyses will be conducted using IBM SPSS Statistics (version 29, IBM Corp., Armonk, NY, USA). Normality checks will be performed via the Shapiro–Wilk test (small to medium samples) supplemented by histograms, Q-Q plots, and skewness/kurtosis assessments.

Reliability Analysis:SWLS questionnaire consistency will be assessed using Cronbach’s alpha (>0.70).Item-total correlations will ensure meaningful contributions to overall scoring.

Inferential Testing:Within-group comparisons: paired samples *t*-test (normal data) or Wilcoxon Signed-Rank test (non-parametric).Between-group comparisons: independent samples *t*-test (parametric) or Mann–Whitney U test (non-parametric).Repeated-measures ANOVA will assess pre- and post-intervention changes, applying Bonferroni corrections for multiple comparisons.

Effect Size and Correlations:Cohen’s d for *t*-tests, Partial Eta Squared (η^2^) for ANOVA.Pearson’s correlation (parametric) or Spearman’s rank correlation (non-parametric) to explore variable associations.

Additional Measures:Homogeneity of variance was tested via Levene’s test.Intention-to-treat (ITT) analysis for participant dropout management, using multiple imputation techniques to mitigate bias.

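### Only the experimental arm must sign a further commitment after learning its allocation, which opens a one-sided exit after randomisation

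*Protocol article*

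**What the plan says.** Section 2.4 (Recruitment) sets out this order of events:

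1. Before enrolment everyone consents: "All participants will provide written informed consent prior to enrollment". At that point "the specific details of the eight-week core training protocol will not be disclosed at this stage to minimize potential bias".
2. Participants are randomised by computer.
3. The experimental group is then told about the training, and its "participants will need to sign additional written consent confirming their commitment to the intervention".
4. For the other arm the text says "The control group will receive written guidelines for a standardized two-day-per-week abs and back routine". It describes no second signature or commitment.
5. For withdrawal or noncompliance, "Replacement participants will be recruited following the same screening and randomization procedures".

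Two other places bear on this. Section 2.3 makes a commitment part of eligibility in both arms: "They must also commit to attending both baseline and final assessments and adhering to the structured eight-week intervention timeline". Section 3.5 lists "Intention-to-treat (ITT) analysis for participant dropout management", with multiple imputation.

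**The concern.** Randomisation makes the arms comparable at allocation. Here a further opt-in follows, in one arm only, at the moment that arm first learns what is asked of it. The demands also differ. Section 3.4.2 describes eight triads over about 30 to 32 minutes, each ending in a high-intensity power exercise. Section 3.4.4 describes 20 to 25 minutes twice a week at moderate to low intensity. The arm with the harder programme is the one with the formal opportunity to decline.

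If the less willing leave at that step, the experimental arm that remains is more motivated than the control arm for reasons unrelated to the training. Exposure varies by outcome:

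- **More exposed:** slam force, the EMG and angular velocity recorded during the slam (all effort-dependent), and the self-reported SWLS.
- **Less exposed:** muscle thickness by ultrasound at rest, and static balance in quiet standing with eyes open.

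**Working it through.** **The plan's own figure.** Section 2.5 gives a minimum of 34 participants for partial η² = 0.06, α = 0.05 and power 0.80. Taking f = 0.25 and an assumed pre-post correlation ρ = 0.5 (not given in the document), the group-by-time F test has λ = f²·N·m/(1−ρ) = 0.0625 × 34 × 2 / 0.5 = 8.5 on (1, 32) degrees of freedom. Power is 0.807, so 34 reproduces. The planned 40 leaves a reserve of 6, which is 6/40 = 15%, or 3 per arm. The consent point does not depend on these figures; the 15% only serves below as a reference refusal rate.

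**Do the safeguards close the exit?**

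- The Section 2.3 commitment covers both arms, but it is given before the training content is known. Section 2.4 still asks the experimental arm to commit again.
- Intention-to-treat with imputation works if a decliner stays in the analysis set and the observed data explain why the outcome is missing. The article does not say that decliners are followed or kept, and refusal through low willingness may not be explained by what was measured.
- Replacements are randomised too, but any who land in the experimental arm meet the same second signature, so the selection repeats.

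**Illustrative size, unadjusted post-test comparison.** All inputs are assumptions. Willingness is standard normal, the least willing share p of the experimental arm declines and is lost or replaced, the outcome correlates r with willingness, and the true effect is zero. Then

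bias (SD) = r · φ(z_p) / (1 − p).

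For p = 0.15 (3 of 20): z = −1.036, φ = 0.233, and 0.233/0.85 = 0.274. With r = 0.3 the bias is 0.3 × 0.274 = 0.082 SD.

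| p declining | r = 0.1 | r = 0.3 | r = 0.5 |
|---|---|---|---|
| 0.05 | 0.011 | 0.033 | 0.054 |
| 0.10 | 0.019 | 0.058 | 0.097 |
| 0.15 | 0.027 | 0.082 | 0.137 |
| 0.20 | 0.035 | 0.105 | 0.175 |
| 0.30 | 0.050 | 0.149 | 0.248 |

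With 20 per arm, SE = √(2/20) = 0.316 SD. The two-sided 5% error becomes 1 − Φ(1.96 − b/SE) + Φ(−1.96 − b/SE), where b is the bias. At p = 0.15 this is 0.051, 0.058 and 0.072 across the three columns. At p = 0.30 it is 0.053, 0.076 and 0.123. Against the planned d = 0.50, the p = 0.15 row is 0.027/0.50 = 5% to 0.137/0.50 = 27%.

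**Group-by-time contrast.** With equal SDs at both visits, the bias in change is (r_post − r_pre) · φ(z_p)/(1 − p). A stable motivation gap (r_post = r_pre) gives zero. If willingness also affects change, for example r_pre = 0.3 and r_post = 0.4 at p = 0.15, the bias is 0.1 × 0.274 = 0.027 SD.

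**The case against.** The strongest reply has several parts.

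- **Pre-post design.** Section 3.5 includes repeated-measures ANOVA, and a stable motivation gap largely cancels in that contrast. This stands. The table applies to the independent-samples post-test comparison that Section 3.5 also lists. A reader might multiply 10–20% refusing by a 0.5–0.8 SD gap (0.10 × 0.5 = 0.05 to 0.20 × 0.8 = 0.16 SD) and conclude that up to about a third of d = 0.50 is bias. The documents support neither input, and the product treats a gap in level as if all of it survived the pre-post contrast.
- **Outcomes.** A reader might infer that every outcome is sensitive to motivation. Resting thickness and quiet-stance balance are neither maximal-effort nor self-reported.
- **Analysis set and replacements.** A reader might infer that only signers are analysed, or that replacements go straight into the experimental arm. No section says the first, and Section 2.4 contradicts the second.
- **Direction.** Controls may also leave on learning their allocation, so a net bias in favour of the programme is plausible but not shown.
- **Condensed article.** Consent material is in Supplementary File S4, which is not at hand and may say how decliners are handled. That could settle the follow-up question. It would not remove the asymmetry that Section 2.4 itself describes.
- **Contamination.** Nothing says controls ever learn the experimental programme. Disclosing it in full to everyone would therefore carry a real cost, since Section 5 already lists controls' outside exercise as a source of variability. This stands and narrows the fix.

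**Conclusion.** The point holds as a design weakness that should be corrected. As written, the procedure puts a formal exit after allocation in one arm, pairs it with replacement, and does not state that decliners are followed and analysed as allocated. It permits one-sided selection; it does not establish that selection will occur.

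The document does not determine the size. For an unadjusted post-test comparison the illustration gives about 0.01 to 0.25 SD, for 5% to 30% declining and a correlation of 0.1 to 0.5 between willingness and outcome. It gives 0.03 to 0.14 SD at 3 of 20 declining, with a two-sided error of at most about 0.07. The group-by-time contrast would be affected less, and not at all if willingness shifts both visits equally. This is a modest threat, concentrated in the slam-based measures and the SWLS.

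**What to change.** 1. Before randomisation, take one consent from everyone that neutrally outlines the time, frequency and intensity demands of both arms and includes a commitment to whichever arm is allocated. Leave exercise-level details until after allocation, to limit contamination.
2. Drop the arm-specific second commitment as a condition of staying in the trial.
3. State that anyone who declines or withdraws after randomisation is invited to the final assessment, is analysed in the allocated arm and is not replaced.

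The cost is a revised consent form and notification of the ethics committee. Controls would learn in outline what the experimental arm does, which is a small contamination risk. The change does not alter the planned sample size, the outcomes or the exercise content. If enrolment has already begun, the third item can still be adopted.

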### 2.5. Sample Size Calculation

To determine the appropriate sample size for this study, a power analysis was conducted using G*Power 3.1 software [43]. The analysis was based on a repeated-measures design with two groups (experimental vs. control) measured at baseline and post-intervention. The following parameters were used: Effect Size (Partial η^2^) = 0.06 (medium effect); Cohen’s d = 0.50. Alpha Level (α) = 0.05 (5% significance threshold); power (1 − β) = 0.80 (80% probability of detecting a real effect); two measurement points (pre- and post-intervention); and two groups (experimental and control). According to the established criteria, the minimum requisite sample size for achieving adequate statistical power was computed to be 34 participants, with 17 participants allocated to each group. The objective of this study is to include and evaluate 40 participants, with 20 subjects in each group, to account for potential participant dropout. This methodological approach ensures that the study can detect meaningful differences in vertical ball strength, muscle activation (EMG), dynamic balance, angular velocity, muscle hypertrophy, and psychological impact (SWLS scores) with sufficient precision.

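### Replacing participants who withdraw or do not comply conflicts with the intention-to-treat handling of dropout and duplicates the 34-to-40 allowance; if the replaced are left out, the comparison is selected on adherence

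*Protocol article*

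**What the plan says.** All references are to the Protocol article.

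- **Allocation (section 2.4).** Participants are screened and consent first. The allocation is then run once: "When the required number of participants is met, a computer-generated randomization process will allocate individuals".
- **Step after allocation (section 2.4).** In the experimental arm only, "participants will need to sign additional written consent confirming their commitment to the intervention". Controls receive written guidelines for a light routine.
- **Replacement (section 2.4).** "Replacement participants will be recruited following the same screening and randomization procedures", with the aim to "adhere to predefined sample size calculations, in the event of participant withdrawal or noncompliance".
- **Sample size (section 2.5).** The calculated minimum is 34 (17 per group). The trial aims to include and evaluate 40 (20 per group) "to account for potential participant dropout".
- **Analysis (section 3.5).** "Intention-to-treat (ITT) analysis for participant dropout management, using multiple imputation techniques to mitigate bias".

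The article does not say whether a replaced participant stays in the analysis. Nor does it say how a late replacement is allocated, beyond the promise of the same procedures.

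**The concern.** ITT and replacement answer the same question in opposite ways. ITT keeps a noncompliant participant in the assigned arm and analyses the outcome. It also keeps a participant who drops out, and the missing outcome is imputed. In neither case is there a vacancy. Replacing someone to hold a fixed number makes sense only if that person no longer counts towards the number.

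Noncompliance is the clearest case. Such a person can still attend the post-test, and section 2.3 requires everyone to commit to both assessments. No data need be missing, yet section 2.4 triggers replacement.

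What is at stake is the randomised comparison. Adherence is observed after allocation and may well differ between arms. The experimental programme is supervised (section 2.2) and includes power work above the anaerobic threshold (section 3.4.2). The control routine is of moderate to low intensity, 20 to 25 minutes twice a week (section 3.4.4). Section 5 itself names adherence as something that may affect outcomes. If non-adherers are swapped out, mainly in one arm, the groups compared are no longer the groups that were randomised.

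**Working it through.** **1. The plan's own sample size**

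Inputs from section 2.5: partial η² and d given as "0.06 (medium effect); Cohen’s d = 0.50"; α of "0.05 (5% significance threshold"; power 0.80; two groups; two time points. The pre-post correlation ρ is not stated, so ρ = 0.5 is assumed.

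For the group-by-time interaction, λ = f² × N × m / (1 − ρ), with 1 and N − 2 degrees of freedom, f = d/2 = 0.25 and m = 2.

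- N = 34: λ = 0.0625 × 34 × 2 / 0.5 = 8.5, power 0.807. The stated 34 reproduces.
- N = 40: λ = 0.0625 × 40 × 2 / 0.5 = 10, power 0.869.
- Sensitivity: the required N is 46 at ρ = 0.3 and 22 at ρ = 0.7.

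**2. The dropout allowance**

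1 − 34/40 = 0.15, and 34/0.85 = 40. The step from 34 to 40 therefore covers the loss of 6 of 40 participants. Within that margin, replacement is not needed to protect the calculated sample size.

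**3. Can 20 per arm be restored by randomising replacements?**

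Replacements that arise after the single allocation cannot be part of it. With independent 1:1 draws, each one enters the vacated arm with probability 0.5. Three vacancies in one arm are all refilled there with probability 0.5³ = 0.125. A guarantee of 20 per arm would require directing people to an arm.

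**4. Size of the bias if replaced participants are left out**

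The document gives neither the share replaced nor the outcome gap. The figures here are assumptions: 15% replaced (3 of 20), in the experimental arm only, with outcomes g = 0.5 to 0.8 SD worse than those of compliers.

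- Mean with everyone kept: 0.85 × C + 0.15 × (C − g) = C − 0.15g, where C is the compliers' mean.
- Mean after replacement by compliers: C.
- Bias = 0.15g: 0.15 × 0.5 = 0.075 SD to 0.15 × 0.8 = 0.12 SD.
- Relative to d = 0.50, if on the same SD scale: 0.075/0.50 = 15% to 0.12/0.50 = 24%.

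**5. Simulation check**

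20 analysed per arm, no true effect, noncompliance in the experimental arm only, replaced participants left out, two-sided t-test at 5%, 20,000 runs.

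| Noncompliance | Compliance-outcome correlation | Bias (SD) | Type I error |
|---|---|---|---|
| 10% | 0.3 | 0.06 | 5.7% |
| 10% | 0.5 | 0.09 | 6.0% |
| 15% | 0.3 | 0.08 | 5.8% |
| 15% | 0.5 | 0.14 | 7.0% |
| 25% | 0.3 | 0.13 | 7.0% |
| 25% | 0.5 | 0.21 | 10.2% |

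With zero correlation, or with the 20 first randomised to each arm all kept, the bias is about 0 and the error about 5%.

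**The case against.** A reader might infer three stronger claims, and the text supports none of them.

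- **That replacements are allocated non-randomly.** The sentence that sets the rule promises the same randomisation procedures. Late entrants could be validly randomised as a separate batch. What is lost is the assurance of 20 per arm, a minor matter of efficiency.
- **That the comparison will drift towards compliers.** This follows only if replaced participants are left out of the analysis. The article does not say so. Keeping and imputing everyone already randomised, and adding new people, would satisfy sections 2.4 and 3.5 literally, with the total rising above 40. The full protocol or the analysis plan, neither shown, may define the analysis set.
- **That replacement can gain nothing.** The allowance covers six losses only, and 34 rests on an assumed ρ of 0.5. An allowance together with a top-up rule is redundant, but that alone is not an error.

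It is also fair that section 2.4 gives no timing. Consent precedes a wait until recruitment is complete, so some withdrawals may occur before allocation, where replacement is harmless.

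These points make the bias conditional. They do not reconcile the text. Noncompliance with an assigned programme arises essentially after allocation, so the rule is not confined to the harmless case. Evaluating 40, with 20 per group, points towards replaced participants not counting. The difficulty is a rule that the article states, not a detail left to another document. As it stands, it would allow the analysed set to be settled once adherence is known.

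**Conclusion.** The conflict stands. Section 2.4 replaces people for events that the ITT and imputation approach of section 3.5 handles without replacement, and it does so on top of the 15% allowance in section 2.5.

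The harm is conditional. If replaced participants are excluded, the comparison is selected on post-randomisation adherence. The illustrative bias of about 0.08 to 0.12 SD rests wholly on assumed figures: 15% replaced, in the experimental arm only, with outcomes 0.5 to 0.8 SD worse. If adherence is unrelated to outcome, or everyone randomised is kept, that bias disappears. Non-random allocation of replacements is not documented. The rule should be changed before the allocation is run, because the present wording does not protect the randomised comparison and the correction is small.

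**What to change.** In section 2.4, limit replacement to people lost before randomisation, and delete it for withdrawal or noncompliance after randomisation. In section 3.5, state that:

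- every randomised participant stays in the ITT set in the allocated arm;
- every randomised participant is invited to the post-test whatever their adherence;
- only missing post-tests are imputed.

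The cost is an amendment of about one sentence in each section. The downside is that fewer than 40 participants may have observed post-test data. The existing allowance covers this for up to 6 losses, since 40 − 6 = 34, the calculated minimum. If more losses are feared, the number randomised at the outset can be raised instead.
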